### Clinical outcomes

The following clinical measures will be evaluated as secondary outcomes in this trial to provide a preliminary estimate of efficacy. All measures will request ratings relevant to the past week.

#### Overall severity of voices

The PSYRATS-AH [56] total score will be the primary clinical outcome measure for this trial, reflecting changes in voice phenomenology, severity and impact. The measure is a structured interview examining 11 dimensions of auditory hallucinations, each rated on a 5-point ordinal scale with total scores summed, with higher scores representing greater overall severity of voice hearing experiences. The scale has demonstrated good reliability and validity with sensitivity to change [56, 68].

#### Negative impact of voices

The Subjective Experiences of Psychosis Scale – Negative Impact Subscale (SEPS [69]) will be used to evaluate the negative emotional and functional impact of the voices on the person. The SEPS is a 45-item self-report scale consisting of three subscales assessing experiences of psychosis. In this case, participants will be asked to select “voices” as the psychotic experience they are rating. The total score of subscale 1 “negative impacts of experiences” (29 items) will be used in the current study. Items are rated on a 5-point scale from 1 (*not at all*) to 5 (*very much*), with scores summed to produce an overall score, with higher scores representing a greater negative impact of the voices on the person. The SEPS has demonstrated good to excellent reliability and validity [69].

#### Emotional distress

The Depression, Anxiety and Stress Scale-21 (DASS-21 [70]) scale is a commonly used measure of depression, anxiety and stress. Each of the 21 items is rated on a 4-point scale from 0 (*did not apply to me at all*) to 3 (*applied to me very much, or most of the time*). Subscale scores are totalled and then doubled to yield an overall score, with higher scores indicating a greater level of overall emotional distress. The scale has demonstrated good reliability and validity in clinical samples [71].

### Process measures

Although the sample size and design preclude mediation analysis, we are including several possible process measures in this trial to evaluate their sensitivity to change. These include two single items using a 0–100-mm visual analogue scale (VAS) measuring confidence in coping with the voices and awareness of factors influencing their fluctuations, and two multiple choice items measuring the range of helpful coping strategies and the consistency of their use. These items reflect the primary intervention aims which may theoretically account for reductions in voice severity and impact.“How confident are you in your ability to cope with the voice/s day to day?”, VAS anchored 0 mm (*not at all confident*) to 100 mm (*very confident*)“I am aware of things which make the voice/s more or less intense”, VAS anchored 0 mm (*not at all*) to 100 mm (*very much*)“Over the past week, how often have you used coping strategies for the voice/s?”, multiple choice: 1 (*never when I heard voice/s*); 2 (*a few of the times I heard voice/s*); 3 (*about half of the times I heard voice/s*); 4 (*most times I heard voice/s*); 5 (*every time I heard voice/s*)“How many helpful coping strategies do you have to manage the voice/s?”, multiple choice: 1 (*I don’t have any helpful coping strategies for the voice/s*); 2 (*I have one or two helpful coping strategies for the voice/*s); 3 (*I have a few different helpful coping strategies for the voice/s*); 4 (*I have several helpful coping strategies for the voice/s*); 5 (*I have a lot of helpful coping strategies for the voice/s*)

### Planned intervention

Participants allocated to the therapy group will receive four face-to-face sessions of approximately 1 h in length, over the 8-week period between baseline and outcome assessments. Sessions are spaced approximately 1–2 weeks apart. In addition, these participants will use a smartphone app between sessions (described below), either their own or one provided to them for the duration of the trial. A breakdown of the intervention details and sequence are provided in Fig. 2, both within and between sessions. The intervention is manualised and will be delivered by the trial coordinator (IB), a trainee psychologist undertaking doctoral studies in clinical psychology, with regular supervision by the PI (NT).

**Fig. 2 Fig2:**
[figure not shown]
Intervention overview

This intervention has been informed by the framework of coping strategy enhancement (CSE [30, 72] and literature on antecedents and coping with voices (e.g. [41, 73–77]). CSE has recently been applied in a brief format targeting distressing voices specifically, supporting feasibility, acceptability and preliminary evidence for improved clinical outcomes [37]. A panel of four individuals with lived experience of voice hearing based in Sussex, UK, were also consulted in the early stages of this research to provide feedback on the design of the intervention and trial, including the wording and schedule of EMA/I surveys.

As an initial phase of the intervention across the first and second sessions, functional analysis will be used to formulate patterns in voice activity, focusing on identifying the antecedents and responses which may give insight into how voices are being maintained. Building from this understanding, the remainder of the intervention will focus on identifying and implementing alternative responses to the voices and their antecedents which may disrupt problematic maintenance cycles associated voice activity and related distress. The therapy can therefore be conceptualised as having two sequential stages: the first involving information gathering and building understanding of daily patterns in voices through functional analysis, and the second involving identification and implementation of individualised coping responses to voices based on the functional analysis. Across these phases, EMA/I will be used to enhance the core aims of the intervention.

#### Stage 1: functional analysis and ecological momentary assessment

Following the first session, participants will complete a 6-day EMA monitoring period during which they complete 10 EMA surveys per day, occurring at semi-random intervals within an individualised 12-h waking period. Each EMA survey will be identical and contain 39 items measuring common antecedents and responses to voices, in addition to voice intensity, distress and impact. A full list of these items and instructions is provided in Additional file 2. The development of the EMA schedule and items involved several iterative stages, including comprehensive literature reviews, consultations with expert clinicians, researchers and lived experience consultants, piloting by researchers, and a small pilot of the intervention with three participants to refine protocols and confirm acceptability of the EMA/I procedure. The purpose of this EMA monitoring period is to provide data which can be analysed to identify potential predictors of voice intensity. In line with recommendations in the literature, at least 33% of the total number of EMA surveys will need to have been completed by the participant in order for analysis of feedback to be conducted [46]. Analysis of the EMA data (produced for the purpose of feedback) will include within-person summary statistics and exploratory multiple regressions conducted on Stata Statistical Software [78], allowing identification of items which predict the intensity of voices. Variables with a standardised beta co-efficient of greater than 0.3 were considered to justify the provision of feedback.

If possible, a feedback sheet will be provided to participants in the second session which will contain the following information: (a) the number of survey responses entered during the monitoring period; (b) average voice intensity and distress scores over the monitoring period; (c) situations, triggers and responses which predicted increased or decreased voice intensity according to multiple regression analysis; and (d) a list of the specific responses to voices reported over the monitoring period and their average reported helpfulness. This feedback will be framed as a guide due to potential limitations in capturing sufficient voice hearing occasions to detect predictors and to avoid inferring causation from correlation data. The feedback will be discussed in the session alongside patterns noticed by the participant during the EMA monitoring period, with the aim of building a functional analysis of voice activity.

### Stage 2: identification and implementation of coping strategies and ecological momentary intervention

Based on the functional analysis conducted across sessions 1 and 2, the therapist and participant will work collaboratively to identify potential coping strategies which may assist the person to cope with their voices and potentially modify patterns in voice activity. Towards the end of the second session, coping strategies will then be chosen by the participant and then coded into the app as personalised coping statements (e.g. “Listen to some relaxing music”). Then, for 10 days following the second session, participants will be sent EMI prompts via the smartphone app of their personalised coping statements. These reminders will occur five times per day, presented semi-randomly within their waking hours. Participants will also be able to view them *on demand* by pressing a button within the app. In addition, participants will complete a short survey each evening asking them about their experiences using the app, the helpfulness of their coping strategies and potential barriers to coping. The latter information is then summarised as feedback and provided to the participant in the following session if possible, with the aim of tracking progress. Based on this discussion, there will be an option to create new coping statements following session 3 or keep the same for a second, identical EMI period. The fourth session will similarly involve reviewing progress and discussing feedback from the app if available, ending with a discussion of how to maintain gains following the end of the intervention.

Fidelity to the intervention protocol will be supported through (a) use of an intervention manual clearly detailing the protocol for each session and procedures between sessions; (b) provision of a participant guide for use during the session which can be used to structure the content and record information; (c) regular supervision of the therapist by the PI, who has expertise in both interventions for voices and the use of digital interventions; and (d) completion of a fidelity checklist following each session by the therapist to record key components of the session.

### Smartphone application

The movisensXS [79] app will be used to facilitate EMA/I in the current study. This app connects with a Web-based platform that allows researchers to program simple and secure EMA/I surveys or prompts that can be individualised for each participant, and download data remotely. The app is downloaded onto the smartphone at the end of the first session, with a schedule of EMA surveys pre-programmed to commence on the following day. At the end of each subsequent session, the app is *updated* (via the Web-based platform) with the participant’s coping strategy reminders, which commence the following day. Use of this survey format was tested by three individuals with persisting voices prior, providing a basis for evaluating the procedures and refining the EMA/I content and design prior to the commencement of the study. Piloting of the movisensXS app was also conducted by the researchers over 7 days to ensure it is reliable for the study purposes.

### Planned analysis

Feasibility of the intervention will be reported as descriptive statistics, focusing on the proportion of participants completing at least 33% of the total number of EMA surveys, the proportion of those in which feedback summaries were able to be produced, and the proportion of EMI reminders viewed. Acceptability will be summarised as means and standard deviations of responses to each item within the satisfaction questionnaire, the proportion of participants giving favourable responses, and representative samples of feedback from open-ended questions. The mean and standard deviation of total scores of the CEQ will also be reported. Feasibility of the trial will be reported descriptively and in figures of referral, screening, consent and attrition, as well as the proportion of fidelity checklist items endorsed as completed. Clinical outcomes will be analysed on an intention-to-treat basis using all available data, adopting statistical approaches to managing missing data if appropriate to the dataset. Results will be summarised as means and/or medians (as appropriate), standard deviations and ranges of all outcome and process measures at T0 and T1 for both groups. Analysis of covariance will be used to estimate T1 between-group differences on all outcome and process measures, controlling for baseline scores. Presentation of the analysis will focus on point estimates and associated 95% confidence intervals rather than statistical significance (*p* values). Standardised effect sizes will be derived using Cohen’s *d*. Secondary analyses will include per-protocol analyses (including only participants who attended at least 50% of therapy sessions) and analyses controlling for baseline moderator variables.

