## Methods/design

## Design

The SAVVy trial is a pilot randomised, controlled, assessor-blinded trial, with two parallel groups, using a 1:1 allocation ratio. Each consenting participant will be randomised to either SAVVy + TAU or TAU alone, following the informed consent and baseline assessment session. TAU will involve continuation of standard treatment provided by the usual care team (usually consisting of medication and case management without psychological treatment). Baseline assessments will occur pre-randomisation (T0) and at a standard period of approximately 8 weeks following randomisation (T1). All participants will be invited to complete the outcome assessment regardless of whether they complete the full course of intervention. Figure 1 displays the Consolidated Standards of Reporting Trials (CONSORT) flow diagram of the study procedure. The protocol was designed in accordance with the Standard Protocol Items: Recommendations for Interventional Trials (SPIRIT) (Additional file 1) and Good Clinical Practice guidelines.

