### Participants

As this is a pilot RCT, power calculations based on effect sizes are not appropriate to inform recruitment targets. Rather, a sufficient sample size is needed for estimating the standard deviation of the outcome measures to inform future power calculations, to determine recruitment and attrition rates, and to evaluate the feasibility and acceptability of the intervention. There is variability across the literature regarding sample size recommendations for pilot RCTs, ranging from 24 to 70 [48–51]. We determined a sample size of 34 (split evenly between groups) would be sufficient to meet the aims of this study, which is within the recommended range and in line with pilot trials of similar interventions (e.g. [28, 52–55]).

Participants meeting the following criteria will be eligible for the study: (1) over the age of 18 years; (2) sufficient conversational English for meaningful participation in the study; (3) experiencing current and persisting auditory verbal hallucinations defined by, over the week preceding the baseline assessment, hearing a hallucinated voice or voices on at least four different occasions *and/or* on at least one occasion and of at least an hour’s duration; we determined this criterion would be the minimum frequency in order to capture their occurrence during the EMA monitoring period; (4) experiencing distress due to the voices (score of 1 or more on item 8 of the Psychotic Symptom Rating Scales-Auditory Hallucinations (PSYRATS-AH [56])); (5) experiencing voices for at least 6 months; and (6) comfortable using a smartphone or willing to learn. Exclusion criteria are as follows: (1) unable to provide informed consent; (2) intellectual disability as assessed by the Wechsler Test of Adult Reading (WTAR [57]) estimated IQ < 70]; (3) voices occur solely in the context of substance or alcohol use; (4) initiation of a new antipsychotic medication within the previous 8 weeks; (5) too distressed or agitated to take part in the study assessed by clinician observation during screening or baseline assessment; (6) current risk of harm to self or others that requires active crisis management.

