### Allocation and blinding

Participants confirmed to be eligible following the baseline assessment will then be subject to random allocation to groups using minimisation procedure, conducted by an experienced researcher independent of the research team using QMinim online software [58]. Randomisation using minimisation will be used as it allows for better balance of patient characteristics across groups, particularly in trials with small sample sizes [59]. In this trial, minimisation will balance whether voices are experienced as non-continuous or continuous (PSYRATS-AH item 1 score ≤ 3 versus 4), because this covariate is predicted to have an effect on treatment response and should therefore be balanced across groups. Allocation will occur within 2 days of the baseline assessment. Participants will then be contacted to alert them to their allocation, with those allocated to the treatment group commencing therapy within 2 weeks of the baseline assessment and those allocated to the control group confirming a date for the outcome assessment.

All outcome assessments will be conducted by a researcher blind to treatment allocation throughout the study. It is not possible to blind participants to their allocation due to the nature of the trial design. Following allocation to the treatment or control arm, and prior to the outcome assessment, participants will be asked not to reveal their group allocation to the researcher conducting the outcome assessment. Outside of the assessments, researchers conducting the outcome assessments are shielded from discussion of participants, and assessments are conducted on different days to the therapy sessions. In the event of an unblinding during the assessment, this will be recorded and addressed by repeating the clinical interview as soon as possible by another blind assessor. Success of blinding will be assessed by asking the assessor to guess which condition the participant was allocated to and indicate their confidence. The PI (NT) is not blinded and responds to any clinical and research issues during the trial that require knowledge of a participant’s condition.

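### The main ANCOVA leaves out the only minimisation factor, so intervals are somewhat too wide if that factor predicts outcome beyond the baseline score

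*Protocol article*

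**What the plan says.** Under Allocation and blinding, the protocol states that "minimisation will balance whether voices are experienced as non-continuous or continuous", defined as PSYRATS-AH item 1 scored at most 3 versus 4. It is the only factor named. The reason given is "because this covariate is predicted to have an effect on treatment response and should therefore be balanced across groups".

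Under Planned analysis, the model for every clinical and process measure is fixed in one sentence: "Analysis of covariance will be used to estimate T1 between-group differences on all outcome and process measures, controlling for baseline scores". The minimisation factor does not appear. The only other adjustment is among the secondary analyses, which include "analyses controlling for baseline moderator variables" without naming a variable.

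The same section says how results will be read: "Presentation of the analysis will focus on point estimates and associated 95% confidence intervals rather than statistical significance". Under Participants the target is 34, split evenly, and the protocol holds that "power calculations based on effect sizes are not appropriate to inform recruitment targets".

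**The concern.** Balancing a prognostic factor at allocation removes most of its contribution to the chance difference between arms. The precision reaches the confidence interval only if the model also contains the factor. If it does not, the factor's variance stays in the residual, and the model-based standard error overstates the real sampling variability. The interval is then too wide and over-covers.

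Adjusting for the baseline value of the same measure recovers part of this, to the extent that the baseline score already carries the factor. What is lost is whatever the factor predicts beyond that score. Because this trial reports its clinical results as estimates with intervals, interval width is the feature affected.

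**Working it through.** **Nothing to reproduce.** The protocol states no SD, effect size, correlation or target precision. The sample size gives 34 / 2 = 17 per arm, and allocation is 1:1.

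**Assumed inputs (none is in the protocol).**
- All 34 participants analysed.
- Proportion with continuous voices 0.4, so the factor's variance is 0.4 × 0.6 = 0.24.
- Within factor level, SD 1 at both times and baseline-outcome correlation 0.5, so the residual variance with the factor in the model is 1 − 0.5² = 0.75.
- The factor shifts the T1 score by d = 0.5, 0.8 or 1.0 SD, with no treatment-by-factor interaction.

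**Residual variance without the factor.**
- Case A, factor unrelated to the baseline score: 0.75 + 0.24d².
- Case B, factor shifts baseline and T1 equally: v − c²/v, with v = 1 + 0.24d² and c = 0.5 + 0.24d².

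**Width ratio, unadjusted to adjusted:** √(residual variance / 0.75) × t(31)/t(30), where t(31)/t(30) = 2.0395/2.0423 = 0.9986.

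| d | A: residual variance | A: width ratio | B: residual variance | B: width ratio |
|---|---|---|---|---|
| 0.5 | 0.8100 | 1.038 | 0.7642 | 1.008 |
| 0.8 | 0.9036 | 1.096 | 0.7833 | 1.021 |
| 1.0 | 0.9900 | 1.147 | 0.7984 | 1.030 |

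The partial correlation of factor and outcome given baseline is √(1 − 0.75 / residual variance). It is 0.27, 0.41 and 0.49 in case A, and 0.14, 0.21 and 0.25 in case B.

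**Simulation of the same cases.** This used biased-coin minimisation with an assumed probability of 0.8, and so includes the small cost of leftover imbalance, which the formula ignores.
- Case A: half-widths of 0.636, 0.674 and 0.705 SD unadjusted against about 0.61 SD adjusted, an excess of about 4%, 10% and 15%. Coverage of the unadjusted interval is about 96% at d = 0.5, rising to about 97% to 98% at d = 1.0.
- Case B: excess of 0.6%, 1.8% and 2.7%, with coverage of 95.4%, 95.1% and 95.6%, which is close to nominal.

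**When adjusting does not help.** Adding the factor narrows the interval only if the sample partial correlation exceeds √(1 − (30/31) × (2.0395/2.0423)²) ≈ 0.19 (leftover imbalance ignored). A separate simulation at N = 34, with factor prevalence 0.3 or 0.5 and factor-baseline correlation 0 or 0.5, gave:

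| Partial correlation | Mean width, adjusted / unadjusted | Runs in which adjusting widened the interval |
|---|---|---|
| 0 | 1.003–1.007 | 71–75% |
| 0.1 | 0.998–1.002 | 65–68% |
| 0.2 | 0.982–0.987 | 46–51% |
| 0.3 | 0.955–0.960 | 25–29% |
| 0.5 | 0.863–0.869 | 2–3% |

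Coverage with the factor in the model stayed between 0.941 and 0.956 throughout.

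**The case against.** **Strength of the factor.** A reader might infer that every between-group interval in this trial is too wide. The protocol does not support that. It calls the factor predictive but gives no strength, and for a measure with a sample partial correlation below about 0.19, adding the factor makes the interval slightly wider. The 4% to 15% range also needs the factor to shift T1 while being unrelated to baseline. Eligibility requires voices for at least 6 months, so a factor that moves a scale at T1 may well have moved it at baseline too. This objection stands and limits the size of the point.

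**Baseline scores already carry the factor.** This is partly right. The baseline PSYRATS-AH total contains item 1 as one of its 11 items. The SEPS, DASS-21 and process measures do not contain it. They may still correlate with it, since the SEPS is completed with voices as the rated experience and the process items concern voices.

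**Meaning of treatment response.** The phrase could refer to effect modification, which a main-effect covariate does not address. That reading is open. It gives no reason to leave the factor out of the main model.

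**Secondary analyses may cover it.** The baseline moderator clause could include the factor, but it names no variable and leaves the main estimate unchanged.

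**Condensed article.** A full covariate list is commonly left to the analysis plan, and the sentence does not forbid further covariates. Even so, the article does state what the main model controls for, and the one factor used in allocation is not there.

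**Conclusion.** The main model as written does not match the allocation scheme, and the mismatch is easily removed. Under the assumed inputs the excess interval width is about 1% to 3% if the factor shifts baseline and T1 equally, and about 4% to 15% if it is unrelated to baseline. Noticeable over-coverage appears only in the second case. If the factor has no effect, adjusting costs 0.3% to 0.7% in mean width. The effect is likely smallest for the PSYRATS-AH total, the primary clinical outcome.

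The error is conservative: there is no bias and no under-coverage. It touches only the clinical and process measures, while the primary outcomes are feasibility and acceptability, reported descriptively, and no power calculation depends on interval width. Severity is minor; this is an improvement at almost no cost. The factor's prevalence, the correlations, the shifts and the minimisation probability are all assumptions.

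**What to change.** Reword the Planned analysis sentence along these lines: *ANCOVA of the T1 score on group, the baseline score and the minimisation factor (PSYRATS-AH item 1 ≤ 3 versus 4), for all outcome and process measures.* Use the same covariates in the per-protocol and moderator-adjusted models.

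The cost is one line of text and one residual degree of freedom (31 to 30 with 34 analysed). Item 1 is already collected at baseline. Making the change before outcome data are analysed avoids a post hoc choice of covariates.
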